### Study Procedures

Alcohol-exposed children, as assessed by maternal interviews, will be randomized into an intervention or a control group with 40 participants in each group, using block randomization. The maternal interview will contain questions regarding alcohol use just before and during pregnancy, including the number of standard units of alcohol consumed, with 3 standard units being the threshold for determining alcohol exposure. A group of 40 unexposed children will be randomized in a group to provide normative data using individual randomization. An overview of the study design is shown in Figure 1. As the participants are drawn from a low-SES and resource-poor environment, the performance of the normative group will serve as a more suitable gauge of cognitive development in the participants’ specific contexts. This will enable us to better interpret the results of the neurodevelopmental assessments.

The SPIRIT schematic is shown in Table 1. Baseline assessments examining cognitive function will be conducted with all 3 groups. The intervention group will then play the FARR game twice a week for 6 months (40 play sessions in total). Post intervention, all 3 groups will receive follow-up cognitive assessments. Data gathered by the game will also be collected from the intervention group. All participants will start the intervention at the same level of difficulty. They will be given the opportunity to play the game during hour-long sessions facilitated by community workers. Play will, however, be self-directed; participants will be encouraged to play but will be allowed to stop at any time during a session. As participants log into the devices, they will be able to continue at the difficulty level they had previously reached.

There are 4 different stages in the game of increased complexity. After 10 trials in a stage, a participant automatically moves on to the next for 10 trials. After the fourth stage, participants start at the first stage again. The difficulty of each stage varies independently based on a participant’s performance. Getting 8 or more correct increases difficulty, getting fewer than 4 correct decreases difficulty, and otherwise the difficulty remains the same.

**Figure 1 figure1:**
[figure not shown]
Overview of study design.

**Table 1 table1:** A trial schedule per the Standard Protocol Items: Recommendations for Interventional Trials schematic.

Timepoint		Study period			
		Enrollment	Allocation		
		−*t*_1_	0	*t* _1_	*t* _x_

**Enrollment**					
	Eligibility screen	X	—^a^	—	—
	Informed consent	X	—	—	—
	Maternal Interview	X	—	—	—
	Allocation	—	X	—	—
**Interventions**					
	FARR^b^ game	—	—	X	—
	No intervention control group	—	—	X	—
	No intervention normative group	—	—	X	—
**Assessments**					
	NEPSY-II^c^ psychometric assessment	—	X	—	X
	Data logged by FARR game	—	—	—	X

^a^Not applicable.

^b^FARR: Foundation for Alcohol Related Research.

^c^NEPSY-II: NEuroPSYchological Assessment, Second Edition.

### Measures

The primary outcome is EF, as measured using the NEPSY-II psychometric assessment score. The secondary outcomes are (1) game performance, as measured in the game log files, (2) reaction time, and (3) increase in the level of difficulty of the task.

Additional demographic data will be gathered during the recruitment process. In addition to alcohol use, data will be gathered on age, gravidity, parity, years of schooling, and household income.

All participants will be evaluated using a selection of subtests of the NEPSY-II that measure executive functioning and working memory. Cognitive function, focusing on EFs, will be measured using the NEPSY-II [36]. The NEPSY-II is a compendium of tests based on the Luria theoretical approach to neurological assessment. It is individually administered and has been shown to be successful in diagnosing a range of childhood disorders. The subtests of this test can also be selected based on the specific domains to be tested [37].

Scores obtained on the subtests of the NEPSY-II are compared with the scores of a normative group based on age. The normative group of the NEPSY-II was selected to closely match the US population between 3 and 16 years of age [38]. This group will differ significantly from the populations of interest in this study; however, the NEPSY-II is relatively insensitive to language and culture differences. Although the results need to be interpreted cautiously, the test remains clinically useful [39]. Insensitivity to language is an important feature as the study sample will be drawn from a predominantly Afrikaans-speaking community, which could affect test performance [40].

In the standardization of the NEPSY-II, subtests showed adequate-to-high internal validity. There was no significant practice effect with re-administration of the test in a short space of time (around 3 weeks), supporting its use for both the pre- and postintervention assessments in this study [41]. Inter-rater agreement was high on both the objectively and more subjectively scored test, and the reliability of subtests remained stable [38]. The inclusion of the third group of children not exposed to alcohol in pregnancy will help guide the interpretation of results.

The NEPSY-II uses separate batteries for children aged 3 to 5 years and children aged 6 to 16 years. Between the ages of 3 and 5 years, not all subtests can be administered. We will be focusing on the subtests that are the same for all participants from 4 to 6 years. Participants who are aged 6 years at baseline and/or at the postintervention assessment will be tested on 4 additional subtests to provide a broader base for comparing game tasks and EFs (see Table 2).

**Table 2 table2:** Subtests to be assessed.

Domain	Attention and executive function	Language	Memory and learning
All ages	Statue	Comprehension of instructions	Memory for designs
All ages	—^a^	—	Narrative memory
All ages	—	—	Sentence repetition
6-year-olds only	Auditory attention	—	—
6-year-olds only	Design fluency	—	—
6-year-olds only	Inhibition	—	—
6-year-olds only	Inhibition naming	—	—

^a^Not applicable.

#### Game Log Files

Additional data will be obtained from the log files generated by the game. The file will record error rates and response times for all tasks. Each child will be allocated a numbered tablet or a profile on a specific tablet, depending on what proves the most practical, and the log file will then be associated with their study number.

#### Sample Size

A total of 120 participants will be recruited and randomized to one of 3 study arms. This is in line with the sample sizes of previous studies looking at FASD and cognitive functioning [9,19,39]. Previous studies of this nature showed a medium effect size [42-45]; however, owing to the differences in method and there not being interventionists involved in the training sample, size calculations were done for a small (*d*=0.2) effect size. With a significance level of .05, 120 participants in 3 groups would yield a statistical power of 0.79 for the repeated measures multivariate analysis of variance (MANOVA) comparing the performance between the 3 groups.

There are approximately 46 ECD centers, and in SBM area, 1593 children aged between 3 and 5 years have enrolled at these centers and 1635 6-year-olds have enrolled in Grade R [46]. Assuming a prevalence rate of 24% of consuming alcohol during pregnancy on the basis of a prevalence study conducted in SBM area [31], it should be possible to reach the desired sample size through 400 interviews.

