### Data Analysis

For the primary hypothesis, the postintervention scaled scores of the intervention group will be compared with those of the control group. This will be done using a MANOVA with group membership as the predictor variable and the scaled scores of the 5 NEPSY-II domains (see Table 1) as outcome variables. Discriminant analysis will be done on the outcome of the MANOVA with the domain scores as predictor variables and group membership as outcome variables.

During further analysis, the baseline NEPSY-II scaled scores of the intervention and control groups will be pooled and compared with the scores of the normative group. This will also be done using a MANOVA with group membership as the predictor variable and the scaled scores of the 5 NEPSY-II domains (see Table 1) as outcome variables. Discriminant analysis will again be done on the outcome of the MANOVA with the domain scores as outcome and group membership as predictor variables.

Postintervention NEPSY-II scaled scores (see Table 1) of the intervention, control, and normative groups will be compared using a MANOVA. Group membership will be the predictor variable, and domain scores will be the outcome variables. Discriminant analysis will be conducted with the domain scores as outcome variables and group membership as predictor variables.

Difference scores between baseline and postintervention assessments will be calculated for all participants. These scores will be compared using a MANOVA with group membership as the predictor variable and changes in domain scores (see Table 1) as outcome variables. Discriminant analysis will be done on the results with changes in domain scores as outcome and group membership as predictor variables.

For the secondary hypothesis, the improvement in game performance will be quantified as how many difficulty levels a participant has successfully completed in each of the 3 different stages of the game. This will then be correlated with performance in the NEPSY-II domain scores in a covariance matrix using the Pearson correlation coefficient. A separate analysis will be done including only 6-year-old children using the additional domains tested (see Table 1).

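### The stated power of 0.79 is for a three-group repeated-measures MANOVA, not for the declared primary test, whose power at d=0.2 is about 0.09 to 0.27

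*Protocol article*

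**What the plan says.** The Sample Size section reports that "size calculations were done for a small (*d*=0.2) effect size" and, at a significance level of .05, claims that "120 participants in 3 groups would yield a statistical power of 0.79 for the repeated measures multivariate analysis of variance (MANOVA") across the three groups. The total is 120 children.

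Under Study Procedures, alcohol-exposed children "will be randomized into an intervention or a control group with 40 participants in each group, using block randomization". The other 40 children are unexposed and form the normative group.

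The Data Analysis section then fixes the primary test: "For the primary hypothesis, the postintervention scaled scores of the intervention group will be compared with those of the control group". The method is a "MANOVA with group membership as the predictor variable and the scaled scores of the 5 NEPSY-II domains" as outcomes. The section goes on to list further MANOVAs: exposed against unexposed children at baseline, all three groups after the intervention, and baseline-to-post difference scores in all participants.

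**The concern.** The analysis that carries the power statement and the analysis that carries the primary hypothesis differ in four ways:

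| | Power statement | Primary test |
|---|---|---|
| Children | 120 | 80 |
| Groups | 3 | 2 |
| Use of baseline | repeated measures | none, post scores only |
| Power given | 0.79 | none |

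The 40 normative children count towards the 120 but add nothing to the intervention-versus-control contrast. A reader of the Sample Size section would take it that the trial has close to 80% power for a small effect on its main question. If the primary test is far weaker than that, the figure misdescribes what the trial can detect.

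**Working it through.** **Inputs.** From the Sample Size section: alpha 0.05, d=0.2, N=120, three groups, stated power 0.79. From Study Procedures: 40 per randomised group and two assessments (baseline and post). From Data Analysis: two groups and five outcomes for the primary test. The article states neither the pre-post correlation ρ nor the inter-score correlation r, so both are varied below as assumptions. No dropout is assumed.

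**Step 1: the plan's 0.79.** Take one outcome, three groups and m=2 occasions.

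- Group-by-time: λ = f²·N·m/(1−ρ), F with 2 and 117 df.
- Between groups: λ = f²·N·m/(1+(m−1)ρ), same df.
- For two groups, f = d/2. So d=0.2 is f=0.1, and f=0.2 is d=0.4.

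| Test | f | ρ | λ | Power |
|---|---|---|---|---|
| Group-by-time or between groups | 0.2 | 0 | 0.04×240 = 9.6 | 0.788 |
| Group-by-time | 0.1 | 0.75 | 0.01×240/0.25 = 9.6 | 0.788 |
| Group-by-time | 0.1 | 0.7 | 0.01×240/0.3 = 8.0 | 0.706 |
| Group-by-time | 0.1 | 0.5 | 0.01×240/0.5 = 4.8 | 0.476 |
| Group-by-time | 0.1 | 0 | 2.4 | 0.258 |
| Between groups | 0.1 | 0.5 | 2.4/1.5 = 1.6 | 0.184 |

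The stated figure can therefore be reached in more than one way. Either 0.2 was entered as Cohen's f with zero correlation, or f=0.1 was used with a pre-post correlation of about 0.75. The article does not say which, if either.

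**Step 2: the declared primary test.** A two-group MANOVA is Hotelling's T². With n=40 per group and five scores, F has 5 and 80−5−1 = 74 df, and λ = (n/2)·D² = 20·D². If every score shifts by d and all pairs of scores correlate at r, D² = 5d²/(1+4r). At d=0.2, 5d² = 0.2:

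| r | D² | λ | Power |
|---|---|---|---|
| 0 | 0.200 | 4.00 | 0.27 |
| 0.3 | 0.091 | 1.82 | 0.14 |
| 0.5 | 0.067 | 1.33 | 0.11 |
| 0.7 | 0.053 | 1.05 | 0.10 |
| 0.9 | 0.043 | 0.87 | 0.09 |

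Simulation gave 0.27 at r=0 and 0.10 at r=0.5.

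If only one of the five scores shifts, D² = 0.04 at r=0, so λ=0.8 and power is 0.09. In that pattern power rises with r: 0.11 at r=0.5, 0.16 at r=0.7 and 0.43 at r=0.9. All of these are below 0.79.

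**Step 3: detectable effect.** For 80% power with F(5,74), λ must be 13.8, so D² = 13.8/20 = 0.69. Then d = √(0.69(1+4r)/5), which is 0.37 at r=0, 0.55 at r=0.3 and 0.64 at r=0.5, on every score.

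**Step 4: a single score, for comparison.** For 40 versus 40 at d=0.2, power is 0.14, and 80% power needs d=0.634. Adjusting for baseline multiplies this by √(1−ρ²): 0.634×0.866 = 0.55 at ρ=0.5, and 0.634×0.714 = 0.45 at ρ=0.7.

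**The case against.** *The repeated-measures analysis is planned.* A reader might infer from the missing label in Data Analysis that the powered model is never run. That goes too far. With two occasions, a MANOVA on difference scores is algebraically the multivariate group-by-time test, and one is planned for all participants. It serves a further hypothesis, however, not the primary one. It also uses five change scores, whereas the reproductions of 0.788 above are for one outcome. When the five-score version was simulated with the intervention group 0.2 SD above both others, power was 0.11 to 0.26 at ρ=0.5 and 0.15 to 0.47 at ρ=0.7, for r from 0.5 down to 0.

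*The 0.79 may be right.* A reader might infer an arithmetic error. The documents do not support that: f=0.1 is the two-group conversion of d=0.2, and with a pre-post correlation of 0.75 it gives 0.788. What stands is that the article does not supply what is needed to tie 0.79 to d=0.2.

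*The sponsor may have meant f=0.2.* Then d is 0.4, and the primary test has power 0.86, 0.48 or 0.36 at r=0, 0.3 or 0.5. Only the zero-correlation case reaches 0.79, and the printed effect size is d=0.2.

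*It is a feasibility trial.* The Overview says so, and the Discussion foresees larger trials. This weakens any demand for 80% power. It does not justify quoting a power that belongs to another analysis next to a primary efficacy hypothesis. A reader might also infer that a non-significant result will be taken as proof that the game fails. The article sets no such rule, so that is conjecture. Nor is the absence of an attrition allowance a fault here, since a condensed article commonly leaves it to the full protocol.

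**Conclusion.** The concern holds as a mismatch between the powered analysis and the primary analysis. The 0.79 describes a three-group repeated-measures test on 120 children, while the primary hypothesis rests on 80 children, two groups and post-intervention scores only. That mismatch is on the page and needs no assumption.

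The size of the gap does rest on assumptions: d=0.2 on all five scores, one common inter-score correlation between 0 and 0.9, and no dropout. Under these, the primary test has power of about 0.09 to 0.27. This is not a strict bound, because other patterns of effect give other values, but at d=0.2 none of those tried came near 0.79.

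**What to change.** Keep the sample size and reword the Sample Size section.

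1. State that 0.79 does not apply to the primary test. If it is kept for the difference-score analysis, give the effect metric (d or f) and the assumed correlation behind it.
2. Add the figure for the primary test, for example: *40 per randomised group gives about 9–27% power at d=0.2 on every score, depending on the inter-score correlation (0.9 to 0), and 80% power for d of about 0.37, 0.55 or 0.64 on every score at inter-score correlation 0, 0.3 or 0.5.*
3. Alternatively, make a baseline-adjusted intervention-versus-control analysis primary and state its detectable effect: about d=0.55 or 0.45 on a single score, at pre-post correlation 0.5 or 0.7. The single-score figures should be quoted only if that analysis becomes primary.

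The cost is a less favourable stated figure. No further participants are needed.

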### Data Analysis

For the primary hypothesis, the postintervention scaled scores of the intervention group will be compared with those of the control group. This will be done using a MANOVA with group membership as the predictor variable and the scaled scores of the 5 NEPSY-II domains (see Table 1) as outcome variables. Discriminant analysis will be done on the outcome of the MANOVA with the domain scores as predictor variables and group membership as outcome variables.

During further analysis, the baseline NEPSY-II scaled scores of the intervention and control groups will be pooled and compared with the scores of the normative group. This will also be done using a MANOVA with group membership as the predictor variable and the scaled scores of the 5 NEPSY-II domains (see Table 1) as outcome variables. Discriminant analysis will again be done on the outcome of the MANOVA with the domain scores as outcome and group membership as predictor variables.

Postintervention NEPSY-II scaled scores (see Table 1) of the intervention, control, and normative groups will be compared using a MANOVA. Group membership will be the predictor variable, and domain scores will be the outcome variables. Discriminant analysis will be conducted with the domain scores as outcome variables and group membership as predictor variables.

Difference scores between baseline and postintervention assessments will be calculated for all participants. These scores will be compared using a MANOVA with group membership as the predictor variable and changes in domain scores (see Table 1) as outcome variables. Discriminant analysis will be done on the results with changes in domain scores as outcome and group membership as predictor variables.

For the secondary hypothesis, the improvement in game performance will be quantified as how many difficulty levels a participant has successfully completed in each of the 3 different stages of the game. This will then be correlated with performance in the NEPSY-II domain scores in a covariance matrix using the Pearson correlation coefficient. A separate analysis will be done including only 6-year-old children using the additional domains tested (see Table 1).

Additional exploratory analyses will be done comparing the demographic information of the 3 groups. These data will be drawn from the maternal interview. Demographic data on the mothers of the alcohol-exposed children (both intervention and control groups) will be pooled and compared with nonalcohol-exposed children to ascertain if there were significant differences between the 2 groups. This will be done using 2 tailed *t* tests for independent samples. To account for family-wise errors, Bonferroni-adjusted values will also be calculated. The variables to be analyzed are age, gravidity, parity, years of schooling, and income. Tobacco and drug use will also be compared among the alcohol-exposed and nonalcohol-exposed groups using a chi-square test.

Further exploratory analysis will be done on the game logs. Reaction time in the various stages of the game will be used to conduct an exploratory factor analysis. Looking for common variations among the various game metrics may unearth underlying variables that better explain which EFs are associated with which game tasks. For each participant, their reaction times for the highest level they successfully complete will be used. Using regularized exploratory factor analysis owing to the small sample size, we can examine whether the conceptually different tasks do in fact target different EFs.

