**Methods:**

We are conducting a randomized controlled trial in the Saldanha Bay Municipal area, evaluating a custom-developed cognitive training program to improve the cognitive function of children aged between 4 and 6 years who were exposed to alcohol in the prenatal stage. Participants will be recruited from local Early Childhood Development centers. Community workers will interview biological mothers to identify alcohol-exposed pregnancies. Alcohol-exposed children will be randomized into an intervention or a control group of 40 participants each using block randomization. A group of 40 children not exposed to alcohol will be included in a normative group using individual randomization. The intervention group will play the game for 6 months (40 sessions). Normative and control groups will receive no intervention. Neurodevelopmental assessments will be done at baseline and upon completion of the study with all participants.

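### The primary intervention-control comparison uses post-intervention scores only, a valid but inefficient choice when every child also has the matching baseline NEPSY-II scores

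*Protocol article*

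**What the plan says.** The Data Analysis section of the protocol article fixes the primary analysis: "the postintervention scaled scores of the intervention group will be compared with those of the control group". The model is a "MANOVA with group membership as the predictor variable and the scaled scores of the 5 NEPSY-II domains (see Table 1) as outcome variables". It has no baseline covariate and no time factor.

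Baseline data are planned for everyone. Study Procedures says "Baseline assessments examining cognitive function will be conducted with all 3 groups", and the abstract says "Neurodevelopmental assessments will be done at baseline and upon completion of the study with all participants". The Measures section restricts the main testing to subtests that are common to ages 4 to 6. Table 2 lists five of these, so each primary outcome has its own baseline counterpart. (The analysis text points to Table 1 for the five scores; I take it to mean the five all-ages subtests in Table 2.)

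Baseline scores are used in two other analyses. One compares pooled exposed children with the normative group at baseline. The other is a separate three-group MANOVA of change: "Difference scores between baseline and postintervention assessments will be calculated for all participants".

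The Sample Size section rests on a different analysis: "With a significance level of .05, 120 participants in 3 groups would yield a statistical power of 0.79 for the repeated measures multivariate analysis". It also states that "size calculations were done for a small (*d*=0.2) effect size".

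**The concern.** In a trial with 40 children per randomised arm, a baseline measurement of the outcome is usually the most useful covariate available. Leaving it out of the primary model has two costs. Outcome variance that baseline could explain stays in the error term. And if the arms happen to differ at baseline, part of that difference stays in the observed treatment effect.

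The change-score MANOVA does not make up for this. It is not the primary test and it pools three groups. It is also less precise than baseline adjustment at any r below 1, and less precise than the post-only comparison if r is below 0.5. The plan therefore gives two differently weighted answers to the intervention-control question and omits the most precise of the standard options.

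At stake is the precision of the main result. There is also a mismatch of method: the power statement is for an analysis that uses both time points, while the declared primary test uses one.

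**Working it through.** **Inputs from the protocol.** Two randomised arms of 40 (Study Procedures: "randomized into an intervention or a control group with 40 participants in each group, using block randomization"); total 120 in three groups, alpha 0.05, effect 0.2 labelled d, stated power 0.79 (Sample Size); five outcomes (Data Analysis, Table 2).

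**Assumptions not in the protocol.** Baseline/follow-up correlation r = 0.3, 0.5, 0.7. Correlation between subtests 0.3 (0.5 as a sensitivity check), taken as unchanged by adjustment. Equal effect d on all five subtests, F tests (two-sided for one score), no dropout.

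**1. The stated power.** For a group-by-time test with 3 groups and 2 time points, λ = f²·N·m/(1−r) on 2 and 117 df. Reading 0.2 as Cohen's f with r = 0 gives λ = 0.04 × 120 × 2 = 9.6 and power 0.788, which matches 0.79. Taking f = 0.1 (the two-group equivalent of d = 0.2) gives the same λ only if r = 0.75; at r = 0 power is 0.26 and at r = 0.5 it is 0.48. The protocol does not say which reading was used. On either, the figure describes a repeated measures test and not the post-only two-group test.

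**2. Chance baseline gap.** SE of the difference in baseline means = √(2/40) = 0.224 SD. The post-only estimate carries r times the gap, so the carried part has SD 0.224r. The chance that the carried part exceeds 0.2 SD is P(|Z| > 0.2/(0.224r)):

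- r = 0.3: about 0.3%
- r = 0.5: about 7%
- r = 0.7: about 20%

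**3. Variance relative to post-only (= 1).** Baseline-adjusted: 1 − r². Change score: 2(1 − r).

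| r | Adjusted | Change score | 40 per arm count as | Detectable d, one score, 80% power |
|---|---|---|---|---|
| post-only | 1 | – | 40 | 0.63 |
| 0.3 | 0.91 | 1.40 | 44 | 0.61 |
| 0.5 | 0.75 | 1.00 | 53 | 0.55 |
| 0.7 | 0.51 | 0.60 | 78 | 0.45 |

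The effective size is 40/(1 − r²), and the detectable d is 0.634 × √(1 − r²).

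**4. Five-outcome power.** λ = 20 × [d²/(1 − r²)] × 5/(1 + 4 × 0.3). The reference distribution is F on 5 and 74 df post-only, and on 5 and 69 df after five baseline covariates. For example, post-only at d = 0.2: λ = 20 × 0.04 × 5/2.2 = 1.82, power 0.138.

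| d | Post-only | r = 0.3 | r = 0.5 | r = 0.7 |
|---|---|---|---|---|
| 0.2 | 0.138 | 0.148 | 0.172 | 0.243 |
| 0.5 | 0.705 | 0.749 | 0.838 | 0.958 |

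With a subtest correlation of 0.5, the d = 0.2 row becomes 0.112, 0.118, 0.135, 0.184, and the d = 0.5 row 0.548, 0.592, 0.691, 0.869.

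**5. What 80% power at d = 0.2 would need on one score.** 393 per arm post-only; 358, 295 and 201 per arm with adjustment at r = 0.3, 0.5 and 0.7.

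**The case against.** The strongest defence is that nothing here is invalid. Randomisation makes the post-only comparison unbiased on average with a correct type I error, and its standard error already allows for chance imbalance. The first hypothesis is framed as a post-intervention difference, and the planned test answers it. The trial calls itself a feasibility study, and a change-score comparison is specified too. All of this stands. It makes the point one of efficiency, but it is no reason to prefer the less precise model when the data are collected anyway.

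Four stronger readings are tempting and not supported:

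- *A chance gap passes in full into the result.* The chance that a baseline gap exceeds 0.2 SD is 37% per subtest, but that describes the gap. Only r times it carries over, so the relevant chance is about 0.3% to 20% for r between 0.3 and 0.7. The 37% would need r = 1.
- *The plan ignores baseline altogether.* That is true of the primary test only.
- *Adjustment would restore adequate power.* At the planned d = 0.2 it does not, and at r = 0.3 the gain is small.
- *The same adjustment should serve every group comparison.* The greater-improvement hypothesis also involves the normative group, which is not randomised against the others and is expected to score higher at baseline. Baseline adjustment there is open to regression to the mean and Lord's paradox, and it answers a different question.

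Nor does the protocol give grounds to demand an age covariate here: the outcomes are scaled scores already referenced to age.

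**Conclusion.** The point holds as a loss of precision in the primary analysis, not as a bias or a validity error. The article states the model explicitly, so this is not a detail left to an unseen analysis plan. For r between 0.3 and 0.7, adjustment removes 9% to 49% of the variance of the intervention-control contrast. The practical value depends on the true effect: slight to modest at the planned d = 0.2, and substantial at a medium effect (d = 0.5) if r is 0.5 or more.

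These sizes rest on an r and a subtest correlation that the protocol does not give. The direction does not: apart from the few degrees of freedom spent, adjustment is at least as precise as either planned alternative. It would also bring the primary test nearer to the two-time-point analysis in the Sample Size section, although the number of groups would still differ.

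**What to change.** Make the primary analysis the intervention-control difference in follow-up scores, adjusted for the matching baseline subtest scores. This can be a MANCOVA on the five subtests or an ANCOVA for each subtest. Use the same adjusted model for the intervention-versus-control part of the greater-improvement hypothesis, so that this question has one answer. Limit the adjustment to the two randomised arms, and keep change scores for comparisons with the normative group. Record the change before follow-up scores are compared by arm.

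The cost is a change of wording and about five degrees of freedom (74 to 69 error df in the five-outcome test). No new data are needed. The sample size text should not claim that adjustment brings power at d = 0.2 to an adequate level.

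### No NEPSY-II model includes the child's age, so any age trend left by the US norms stays in the scores, chiefly in the comparisons with the normative group

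*Protocol article*

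**What the plan says.** The Data Analysis section describes four NEPSY-II MANOVAs: intervention versus control after the intervention (primary), pooled exposed arms versus normative group at baseline, all three groups after the intervention, and difference scores across all three groups. In the primary analysis, "the postintervention scaled scores of the intervention group will be compared with those of the control group", by a "MANOVA with group membership as the predictor variable and the scaled scores of the 5 NEPSY-II domains" as outcomes. The rest also have group as the only predictor, and the last takes "changes in domain scores (see Table 1) as outcome variables". None includes the child's age.

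Age enters only through scoring. Measures says: "Scores obtained on the subtests of the NEPSY-II are compared with the scores of a normative group based on age". That reference group "was selected to closely match the US population between 3 and 16 years of age", and the article adds: "This group will differ significantly from the populations of interest in this study". It then softens this by saying that the test depends little on language and culture and is still of clinical use if read with caution.

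Under Study Procedures the 40 unexposed local children are included because "the performance of the normative group will serve as a more suitable gauge of cognitive development". Under Recruitment they are picked by random number tables from unexposed children, with no age matching stated. The exposed children are allocated in blocks of 8, with no age stratification stated.

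The age that the Data Analysis section does list stands among the mothers' demographic variables. It is compared by t test and adjusts nothing.

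**The concern.** Scaling by age removes the effect of age only if children in the study gain with age at the rate of the norm group. A constant difference in level would do no harm, because it shifts every child alike. A difference in growth rate would leave a trend across the eligible ages of 4 to 6 years. The article gives reason to ask whether the US reference fits, but no model is set up to absorb a misfit.

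The consequence differs by comparison. Between the randomised arms, age is balanced in expectation, so a residual trend adds noise and leaves room for chance imbalance. Against the normative group there is no randomisation. A difference in mean age would then be read partly as an effect of alcohol exposure (hypothesis 2) or as distance from normal development after training (hypotheses 3 and 4).

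**Working it through.** **The plan's figures.** The article gives no figure for age. Its planning figures are *d* = 0.2, significance level .05, 120 children in three groups and power 0.79. The power can be matched but not confirmed, because the correlation between visits is not stated. Noncentrality *f*² × 120 × 2 / (1 − ρ) equals 9.6, and power 0.788, for *f* = 0.2 with ρ = 0 and also for *f* = 0.1 (that is, *d* = 0.2) with ρ = 0.75. Nothing below depends on it. Only *d* = 0.2 serves as a yardstick.

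**Assumptions.**
- Ages uniform from 4 to under 7 years, since Measures expects some children aged 6 at baseline. Variance 3²/12 = 0.75, SD 0.87 years.
- Residual slope of scaled score on age of 0.2 to 0.4 SD per year. The documents give no value.
- Group sizes 40, 40 and 40, from Sample Size and Study Procedures.

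**Baseline normative contrast (80 versus 40).**
- SE of the difference in mean age = 0.866 × √(1/80 + 1/40) = 0.866 × 0.194 = 0.17 years.
- One-SE gap: 0.168 × 0.2 = 0.03 SD; 0.168 × 0.4 = 0.07 SD.
- 95% limit: 1.96 × 0.168 = 0.33 years, giving 0.07 to 0.13 SD, or about one third to two thirds of *d* = 0.2.

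**Contrasts of 40 versus 40 (intervention versus control, or one arm versus the normative group).**
- SE = 0.866 × √(2/40) = 0.19 years; 95% limit 0.38 years.
- Shift at that limit: 0.08 to 0.15 SD.

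**Precision in the primary comparison.**
- Share of variance due to age = *s*² × 0.75 / (1 + *s*² × 0.75).
- *s* = 0.2: 0.03/1.03 = 2.9%. *s* = 0.4: 0.12/1.12 = 10.7%.
- Residual SD after adjustment: √(1 − 0.029) = 0.985 and √(1 − 0.107) = 0.945.
- Power for one outcome, 40 per arm, two-sided .05, *d* = 0.2: 0.143 unadjusted, 0.146 to 0.155 adjusted. The gain is smaller again if baseline score is also a covariate.

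**Narrower age range.** If ages run only from 4 to 6.0 years, the variance is 2²/12 = 0.33 and the SD 0.58 years. All the shifts fall by one third, and the variance share becomes 1.3% to 5.1%.

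**Change scores.** A linear slope adds slope × interval to each child's difference: 0.5 × 0.2 to 0.5 × 0.4, or 0.10 to 0.20 SD over six months. With a common interval this is the same in every group and cancels.

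**The case against.** The article does not say that the test misfits these children. It says that the norm group differs, and then defends the instrument. No passage says that growth with age differs, so the harmful mechanism is possible but not shown. The groups share one eligibility range and come from the same centres, so a large age gap is not expected. The normative comparisons are not the primary analysis. The local group is used as promised, as an aid to interpretation; the article never undertakes to re-norm the scores. All of this stands and limits the size of the point. It does not remove it: the models are stated, the article itself questions the reference group, and the normative contrasts have no protection by design against an age difference.

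Two stronger readings are tempting. First, because "The NEPSY-II uses separate batteries for children aged 3 to 5 years and children aged 6 to 16 years", a reader might infer that the change of battery at 6 contaminates the main scores and adds error to the change scores. The documents do not support this. Measures focuses on subtests given at every age from 4 to 6. Table 2 lists five of them, which matches the five outcomes of the MANOVAs, and the four subtests for 6-year-olds go to a separate analysis. Nothing shows that items or norms of the common subtests change at 6.

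Second, a reader might suppose a half-year age gap, which would give 0.10 to 0.20 SD and could equal the whole planned effect. But 0.5/0.168 is about 3 standard errors. It would need a systematic age difference, and no passage suggests one.

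**Conclusion.** The point holds as a modest weakness of the stated models. The only age correction is a US norm whose reference group the article itself calls different from these children, and no baseline or post-intervention model adjusts for what that correction may leave.

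The randomised primary comparison is not biased. At the assumed slopes, age would explain about 3% to 11% of the variance, and power at *d* = 0.2 would hardly move. The stronger reason to act lies in the normative comparisons, where chance alone could shift the baseline contrast by 0.03 to 0.07 SD (one standard error) or 0.07 to 0.13 SD (95% limit). A systematic age difference would add to this, but none is documented.

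These sizes rest on the assumed slope and age distribution. If growth with age follows the US norm, they are zero. The change-score analysis is not affected by a linear trend when the interval between tests is the same in all groups.

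**What to change.** In Data Analysis, add the child's age at assessment, centred and linear, as a covariate in the baseline and post-intervention NEPSY-II models (a MANCOVA in place of the MANOVA). The models that include the normative group have priority. Report mean age by group beside those comparisons, so that a reader can see whether a gap exists. The change-score model needs no age term for this reason, and no battery covariate is called for.

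The cost is one degree of freedom per model and one sentence. No new data are needed, because age at test is already required for scoring. The Results section says that most recruitment is complete, so matching or stratifying by age is largely out of reach and the analysis is the practical place for the change. It should be fixed before group comparisons are seen.
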